#### Inclusion criteria and common factor

We will use the short version of the Brief Symptom Inventory (BSI-18) [68] to assess clinical level of psychopathology. A total scale score of the BSI (*Global Symptom Index*, GSI) of T > 60 indicates a significant level of psychopathology. In psychotherapy, treatment expectancies have been shown to predict change in outcome variables (e.g., depression, [29, 55]). For that reason we will examine the associations between athletes’ expectancies (after the randomization) and subsequent changes in the primary and secondary outcome variables.

### Statistical analysis

All analyses will be conducted as intent-to-treat. To assess if randomization is successful in balancing demographic characteristics across the treatment groups, we will compare age, use of psychological skills, mindfulness, and performance level using Student’s t-tests. Two-way (group x time) repeated measures ANOVAs will be used to answer the question regarding whether the intervention (independent variable) had an effect on the primary and secondary outcome measures (dependent variables). Significant overall effects will be followed up with post hoc tests and contrasts between intervention programs (e.g., PST and MI together compared to the WC group). Significance levels will be set at *p* = .05. If there are significant differences between different intervention sub-groups, we will perform multilevel analyses. To test the mediation and moderation models, we will follow the requirements for mediation and moderation suggested by Hayes [36]. The first three authors of this manuscript will have access to the full dataset.

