**Methods/Design:**

The presented trial uses a randomized controlled design with three groups, comparing PST, MI and a waiting list control condition. Both group interventions will last 5 weeks, consist of four 2 h sessions and will be administered by a trained sport psychologist. Primary outcome is functional athletic behavior assessed using ambulatory assessment in a competition/game. As secondary outcomes competition anxiety, cognitive interference and negative outcome expectations will be assessed. Assessments are held at pre- and post-intervention as well as at 2 months follow up. The study has been approved by the ethical committee of the Swiss Federal Institute of Sport.

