## Method

### Participants and power analysis

The target group are elite, sub-elite, and recreational athletes from four sports (curling, volleyball, i.e., indoor and beach, tennis, and hockey, i.e., floorball and ice hockey). We chose these sports because they are suited to sample comparable short sequences (see primary outcome below) within a game or a competition, as opposed to, for example, soccer. Athletes who are members of the respective Swiss national sport associations will be contacted and offered the opportunity to participate. Criteria for exclusion are a likely mental disorder, significant previous experience with PST or MI, less than 4 h of athletic training per week, or being younger than 18.

The sample size calculation is based on differences between the waiting-list control group (WC) and one of the treatment groups (PST or MI) after the intervention. Based on previous research, we assume medium effect sizes of d = .6 [39]. Testing one-sided, given that α = .05 and a power of 80 %, we would need 108 participants (36 for each group) to be able to detect the effect.

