**Fig. 1 Fig1:**
[figure not shown]
Participant recruitment and flow through the study

Table 1 gives an overview of the assessment/measures. PST and MI participants will be assessed at pre-intervention (time 1), post-intervention (time 2), and at 2 months follow-up (time 3). WC participants will be assessed at time 1 and 2, and will then be randomly assigned to the PST or MI intervention. Participants will complete a series of questionnaires at all assessment time points. Participants names will be coded in the data file for anonymization and the code key will be stored in a different file. Since it is not possible to mask condition assignment for the participants or the experimenter, we will assess and control for outcome expectations regarding the assigned intervention in order to control for potential effects on outcomes (see recommendations by Boot et al. [10]).

**Table 1 Tab1:** Instruments assessing inclusion and exclusion criteria, primary/secondary outcomes, moderators, mediators, and common factor

Concept	Measurement (items)^a^	Time points^b^			
		T0	T1	T2	T3
Inclusion/exclusion criteria					
Clinical level of psychopathology	BSI-18 (18)	x			
Experience with PST/MI	-	x			
Primary outcome measure					
Functional athletic behavior	Ambulatory assessment		x	x	x
Secondary outcome measures					
Psychological variables					
State anxiety	CAI-S (scales cognitive and somatic anxiety, 8)		x	x	x
Cognitive interference	TOQS (17)		x	x	x
Negative outcome expectation	CAI-S (confidence scale inversed, 4)		x	x	x
Athletic performance					
Objective measures	E.g., win/lose, points scored		x	x	x
Subjective measures	Self-rated measures of performance		x	x	x
Mediators					
Use of psychological skills	TOPS (scales self-talk, imagery, goal-setting, relaxation and activation, 20)		x	x	x
Ability to control thoughts and emotions	TOPS (scales negative cognitions and emotional control, 8)		x	x	x
Mindfulness	FFMQ-SF (24) & AMQ (16)		x	x	x
Acceptance of (unpleasant) experiences	SEC-27 (acceptance scale, 3) & AAQ-II (inversed, 9)		x	x	x
Defusion	EQ (decentering scale, 7), DSS (12)		x	x	x
General attention	ANT		x	x	x
Moderators					
Task difficulty	-		x	x	x
Importance of game/competition	-		x	x	x
Demographic characteristics	-	x			
Task- & ego-orientation	TEOSQ (13)		x		
Self-esteem	RSC (10)		x		
Self-compassion	SCS short form (12)		x		
Common factor & practice time					
Athletes’ expectancy of the intervention	- (3)		x		
Practice time	Practice sheets			x	x

^a^

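### The group × time ANOVAs do not fix which arms and visits they cover, and deliver the promised intent-to-treat analysis only if missing values are imputed or a mixed model replaces them

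*Protocol article*

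**What the plan says.** The Statistical analysis section states the principle, "All analyses will be conducted as intent-to-treat", and then the method for primary and secondary outcomes: "Two-way (group x time) repeated measures ANOVAs will be used to answer the question" of whether the intervention had an effect. Significant overall effects are followed by post hoc tests and contrasts, with both active programmes against the waiting list as the example. The levels of the group and time factors are not given. The section mentions one other model: "If there are significant differences between different intervention sub-groups, we will perform multilevel analyses".

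The abstract (Methods/Design) describes the visits without distinguishing arms: "Assessments are held at pre- and post-intervention as well as at 2 months follow up". Table 1 likewise marks the outcomes at T1, T2 and T3 with no exception for an arm. The text under Study design and group allocation does distinguish them. PST and MI athletes have all three visits, but "WC participants will be assessed at time 1 and 2, and will then be randomly assigned to the PST or MI intervention".

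The sample size (Participants and power analysis) rests on "differences between the waiting-list control group (WC) and one of the treatment groups (PST or MI) after the intervention", with d = .6, one-sided α = .05 and 80% power, giving 36 per group and 108 in total.

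**The concern.** Two stated choices do not sit together.

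- **Intent-to-treat against the named method.** In its classical form, a repeated-measures ANOVA needs a value at every level of the time factor. An athlete with T1 but no T2 contributes nothing, even to a two-visit version. FAB is rated only during an actual game or match, so an athlete without a T2 match has no T2 value. The one model in the plan that could keep such athletes, multilevel analysis, is triggered by sub-group differences and not by missing values.
- **An open time factor.** The waiting list supplies no untreated value at T3. The plan does not say whether the ANOVAs use two visits or three, or which arms enter each.

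If athletes who leave differ from those who stay, and differently by arm, a completers comparison is biased. If arms and visits are left open, they can be chosen after the data are seen, and a T3 result could be read as an effect against control, which this design cannot estimate.

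**Working it through.** **1. The plan's own figure.** Inputs from Participants and power analysis: d = .6, one-sided α = .05, power 80%. For two equal groups of n, the noncentrality is d·√(n/2) with 2n − 2 degrees of freedom.

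- n = 35: .6·√17.5 = 2.510; power .800 when rounded, but just under .80 (.7996).
- n = 36: .6·√18 = 2.546, critical t(70) = 1.667; power .809.

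So 36 per group and 3 × 36 = 108 reproduce exactly. The same 36 gives .709 two-sided. The intervention description builds six groups of six per condition, 6 × 6 = 36, so the planned number equals the powered number, with no margin for loss.

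**2. Which ANOVA fits the visits.**

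| Arm | T1 | T2 | T3 |
|---|---|---|---|
| PST | yes | yes | yes |
| MI | yes | yes | yes |
| WC, as untreated control | yes | yes | none |

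- Three groups × three visits: the WC–T3 cell is empty, so this model cannot be estimated with WC in it.
- Three groups × two visits (T1, T2): all cells are filled, and it contains the powered comparison.
- PST against MI × three visits: all cells are filled, with no control arm.

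The second and third together fit the schedule. The plan does not say that these are the ones meant.

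**3. Power if only completers are analysed.** The documents give no rate of loss, so a range is assumed. Completers per arm are 36 × (1 − loss), rounded down; the power formula is that of step 1.

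| Assumed T2 loss | Completers per arm | Power, one-sided | Power, two-sided |
|---|---|---|---|
| 0% | 36 | .809 | .709 |
| 5% | 34 | .789 | .684 |
| 10% | 32 | .767 | .656 |
| 15% | 30 | .743 | .627 |
| 20% | 28 | .716 | .597 |
| 30% | 25 | .672 | .547 |

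Without rounding, 15% loss leaves 30.6 per arm, with power .750 one-sided and .636 two-sided. Step 4 uses this value.

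**4. What a mixed model recovers.** Take two visits, n = 36 at T1, m = 30.6 at T2, and a T1–T2 correlation ρ (assumed). The likelihood estimate of an arm's T2 mean has variance (σ²/m)·[1 − ρ²(1 − m/n)], where 1 − m/n = .15. The effective sample size per arm is therefore m / (1 − .15ρ²).

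| ρ (assumed) | 1 − .15ρ² | Effective n | Power, one-sided |
|---|---|---|---|
| .3 | .9865 | 31.0 | .755 |
| .5 | .9625 | 31.8 | .765 |
| .7 | .9265 | 33.0 | .779 |

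Against .750 for completers and .809 with no loss, the gain is .005 to .029 (about 0.5 to 3 points). Most of the fall comes from the missing T2 values themselves, not from the choice of ANOVA. T3 values could add a little in PST and MI, but WC has none.

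**The case against.** The strongest reply is that the plan does not say what a critic may read into it. A reader might infer that the ANOVA contradicts the three-visit schedule and would discard the whole control arm, 36 of 108 athletes. The documents do not support that. The method is named in the plural, no time levels are fixed, the waiting list's two visits are stated openly, and the sample size refers to the comparison after the intervention, which is T2. No effect against the waiting list at two months is claimed in the objectives. The abstract is a summary, and Table 1 lists instruments by visit, not by arm. This part of the reply stands.

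A reader might also infer that the plan orders athletes with a missing visit to be deleted. It does not. That is the method's default, imputation before ANOVA would satisfy intent-to-treat, and an article may leave missing-data detail to a fuller plan. This stands too, and the absence of a missing-data paragraph is not the point. What remains is that the article does commit itself to a method which, unaided, does not deliver the principle stated in the same section, and it ties the model that could do so to a different trigger.

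Finally, a mixed model does not restore most of the lost power, and it does not remove bias when loss depends on the unobserved T2 value. Both statements are correct and limit what the change can be said to achieve.

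**Conclusion.** The point holds as a weakness in how the analysis is fixed, not as a contradiction. The named ANOVAs give an intent-to-treat analysis only with imputation or a different model, and the arms and visits they cover are left open although no untreated control exists at T3. The powered comparison can be tested on T1 and T2, so the control arm is not necessarily lost.

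The size is moderate. For assumed T2 losses of 5% to 30%, completers-only power is about .79 to .67 one-sided, against .809 with complete data. At 15% loss a mixed model reaches about .755 to .779 instead of .750. These figures rest on the plan's d = .6, on a plain comparison of T2 means between two arms, on equal loss in both arms, and on T1–T2 correlations of .3 to .7. The rates of loss and the correlations are assumptions. The better reasons to change are less bias when loss is missing at random given the observed data, consistency with the stated principle, and a clear limit on what T3 can show.

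**What to change.** In the Statistical analysis section:

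1. Name FAB at T2 as the primary outcome and time point, matching the comparison used for the sample size.
2. Estimate PST–WC and MI–WC at T2 from a likelihood-based linear mixed model that uses all available data from every randomised athlete, analysed as randomised. Do not make this model conditional on a test of sub-group differences.
3. Use waiting-list data from T1 and T2 only, so that nothing recorded after these athletes move to PST or MI counts as control.
4. Use T3 for PST and MI only. State that it shows maintenance and the PST–MI comparison, and not an effect against control.
5. Add the waiting-list exception at T3 to Table 1 and the abstract's description of visits.

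The cost is a change of model, a few sentences and slightly more analysis work. No new data, visits or athletes are needed. The change should not be presented as a remedy for power, because the sample still has no margin for lost T2 values.

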### Study design and group allocation

Figure 1 shows an overview of the procedure (parallel group design). After a first contact and checking for inclusion and exclusion criteria (time 0), athletes will be stratified for gender, sport, and performance level, then randomly assigned to either the PST group, the MI group, or the WC group, and will be informed about their experimental condition. Members of the same team (i.e., curling, volleyball, or hockey) will be assigned to the same intervention group. For randomization, a computer-generated random-number sequence will be prepared in advance and sealed in opaque, consecutively numbered envelopes by an independent researcher. An independent researcher will open the envelopes in sequence based on client number, to determine the participant’s assignment to the groups.

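### The group-by-time ANOVA compares change scores against the waiting list; adjusting for baseline FAB would be more precise with data already collected

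*Protocol article*

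**What the plan says.** The Statistical analysis section fixes the effect test for primary and secondary outcomes: "Two-way (group x time) repeated measures ANOVAs will be used to answer the question regarding whether the intervention (independent variable) had an effect". It names no baseline covariate, so pre-intervention FAB enters as one level of the repeated outcome.

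Under Study design and group allocation, "athletes will be stratified for gender, sport, and performance level, then randomly assigned". None of these three factors is in the two-way model. They reappear only as candidate moderators. The one adjustment mentioned is for expectations about the assigned intervention.

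The same section gives the timing for the control arm: "WC participants will be assessed at time 1 and 2", after which these athletes are randomised to one of the interventions.

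The sample size in Participants and power analysis uses the difference between one active arm and WC after the intervention: "we assume medium effect sizes of d = .6", one-sided α of .05, power 80%, 36 per group.

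Baseline data have one further use. The stated purpose is "To assess if randomization is successful in balancing demographic characteristics across the treatment groups", and for this "we will compare age, use of psychological skills, mindfulness, and performance level using" Student's t-tests. No consequence is attached to the results.

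**The concern.** With two time points, the group-by-time interaction is the same as a comparison of mean change from T1 to T2. A change score subtracts the whole baseline value, whatever its correlation with the outcome. When the correlation is modest, this adds noise; below .5 it does worse than ignoring baseline altogether. ANCOVA estimates how much of the baseline to subtract.

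A modest correlation is plausible here. FAB is three self-rated items over three or four sequences of a single game, and the protocol itself treats opponent strength and the importance of the game as influences on the result. At stake is the power of the primary comparison, because the sample size calculation makes no allowance for the noise that a change score adds.

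The baseline t-tests raise a smaller concern. They include performance level, which is a stratification factor, and leave out baseline FAB. With random allocation, a p-value on a baseline variable does not tell whether the allocation procedure worked.

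**Working it through.** **Inputs.** From the protocol: d = .6 (SD set to 1), one-sided α = .05, 36 per arm, and T1 and T2 as the only time points common to all three arms. Assumed: equal SDs at T1 and T2, athletes independent, and r = .3, .5 or .7, because the protocol gives no r.

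**The plan's own figure.** A two-sample t-test on post scores, one-sided .05, 80% power and d = .6 needs 36 per arm by the noncentral t (35 by the normal approximation). Power at 36 is 80.9%. The stated 108 is reproduced, and it assumes a post-score comparison.

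**Variance of the effect estimate, relative to post scores alone.**
- Change score (group by time): 2(1 − r)
- ANCOVA: 1 − r² = (1 − r)(1 + r)
- Ratio, change score to ANCOVA: 2/(1 + r), above 1 for every r < 1

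The change score equals post-score precision when 2(1 − r) = 1, that is at r = .5. Below that it is worse.

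**Power, one active arm against WC.** The noncentrality is .6 / √(v × 2/36), with v the relative variance. At r = .3, v is 1.40 for change and 0.91 for ANCOVA, giving 2.15 and 2.67. There are 70 degrees of freedom, one fewer for ANCOVA.

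| r (assumed) | v, change | v, ANCOVA | Ratio | Power, change | Power, ANCOVA | n per arm for 80%, change / ANCOVA |
|---|---|---|---|---|---|---|
| .3 | 1.40 | 0.91 | 1.54 | 68.6% | 84.1% | 49 / 32 |
| .5 | 1.00 | 0.75 | 1.33 | 80.9% | 89.7% | 36 / 27 |
| .7 | 0.60 | 0.51 | 1.18 | 94.6% | 97.0% | 22 / 19 |

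Simulation (20,000 runs per r) gave standard errors of 0.278 against 0.226, 0.237 against 0.206, and 0.182 against 0.169. Both estimators were centred on .6, so neither is biased. Six further degrees of freedom for the strata change power by about 0.1 point.

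**Power, PST and MI together against WC.** This is the contrast that the protocol gives as its example: 72 against 36, two-sided .05, noncentrality .6 / √(v × (1/72 + 1/36)).

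| r (assumed) | Change | ANCOVA |
|---|---|---|
| .3 | 69% | 86% |
| .5 | 83% | 92% |
| .7 | 96% | 98% |

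**Baseline t-tests.** A t-test compares two groups, so three arms need three pairwise tests per variable. For one freely varying variable, the chance of at least one p < .05 among the three is about 12.2% (simulated, 36 per arm). For the three unstratified variables (age, skills use, mindfulness), taken as independent, it is 1 − (1 − 0.122)³ ≈ 32%.

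**The case against.** The strongest reply is that both analyses are valid, so the choice is one of preference. It is true that nothing here is biased or contradictory. But ANCOVA is the more precise at every r below 1, and the sample size rests on a precision that the planned test may not reach.

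A second reply is that r is unknown. Averaging several items and sequences may raise it, and no text says that opponents differ between T1 and T2. This stands: the direction of the loss is certain, its size is not, and at r = .7 the gain is small.

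A third reply is that gender, sport and performance level do not change between T1 and T2, so their stable effects largely cancel in a change score, and a condensed article may leave a covariate list to a fuller document. This also stands. A reader might infer that leaving the strata out does serious damage to the planned test; the document gives no evidence that they predict change in FAB.

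Three further inferences go too far:
- Two-sided pairwise power for the change score at r = .5 is 70.9%, which might be blamed on the missing covariate. The drop from 80.9% comes from the switch from one-sided to two-sided testing, a separate matter.
- Counting all four baseline variables gives a false-alarm chance of about 40%, but this treats performance level as free to vary although it is stratified.
- The t-tests might be read as a substitute for adjustment. The text calls them only a check on randomisation and ties no decision to them.

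**Conclusion.** The point holds as a loss of efficiency. Whatever r is, the planned comparison with WC carries 2/(1+r) times the variance of ANCOVA: 1.54, 1.33 and 1.18 at r of .3, .5 and .7. On the protocol's own one-sided terms the planned test falls below 80% power somewhat under r = .5 (74.4% at .4, 68.6% at .3), while ANCOVA stays above 80% throughout. The pooled contrast shows the same pattern with a smaller shortfall.

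The sizes rest on assumed r, equal SDs and independent athletes. Teammates share an arm and sessions run in groups of six, so true power is likely to be lower for both methods; ANCOVA does not address that. The strata and the baseline t-tests are secondary. The change should be made, but the trial's validity does not depend on it.

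**What to change.** Make the primary model T2 FAB on arm, T1 FAB, gender, sport and performance level, together with the term for clustering. The strata belong in it because they were used in allocation, and because adjusting for T1 FAB does not remove their stable effects as fully as differencing does. Use the same form for each secondary outcome that has a T1 value, with that value as the covariate. Delete the baseline t-tests and present a descriptive baseline table by arm that includes T1 FAB.

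The cost is a change of wording and a few degrees of freedom. Every variable is already collected, and the sample size need not change on this account.

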## Current study

This study tries to bridge some of the gaps in the current research by conducting a high-quality RCT based on the CONSORT criteria [66], comparing a PST, a MI, and a waiting-list control group. We will use an outcome variable (FAB) that allows us to compare different sports and allows for examining the success of the interventions regardless of external factors, such as being in shape or training load. This way, we will be able to determine whether PST and MI are effective. Furthermore, by investigating the role of mediators and moderators, we will gather evidence about mechanisms of change and for whom each intervention is most beneficial. Our primary interest is to determine the effect of PST and MI on FAB. In order to examine the effects of a broader range of outcomes, factors that may negatively influence FAB (i.e., negative outcome expectations, competition anxiety, and cognitive interference) and objective and subjective measures of performance will be assessed as secondary outcome variables.

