#### Secondary outcome measures

Secondary outcomes are *negative outcome expectancies* (assessed directly before the game or match) as well as *somatic* and *cognitive competition anxiety* (directly after the game or match), which are all measured by the respective scales of the Competition Anxiety Inventory State (CAI-S) [11]. *Cognitive interference* (directly after the game or match) is measured by the Thought Occurrence Questionnaire for Sport (TOQS) [61]. In addition, we will assess objective (win/lose, performance indicators relevant for the sports discipline, such as shot percentages, points scored, winners/unforced errors, and goals/assists) and subjective (self-rated) measures of performance.

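### Win/lose is tested by an ANOVA with athletes as the apparent unit, although team-mates in one arm share a single result, so false positives are likely to be well above 5%

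*Protocol article*

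**What the plan says.** All of this is in the protocol article.

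- **Statistical analysis** names one test for effectiveness: "Two-way (group x time) repeated measures ANOVAs will be used to answer the question" whether the intervention "had an effect on the primary and secondary outcome measures (dependent variables". No other model is named for any outcome in that set.
- **Current study** says that "objective and subjective measures of performance will be assessed as secondary outcome variables". **Secondary outcome measures** gives the objective ones: "win/lose, performance indicators relevant for the sports discipline, such as shot percentages, points scored, winners/unforced errors, and goals/assists".
- **Study design and group allocation**: "Members of the same team (i.e., curling, volleyball, or hockey) will be assigned to the same intervention group".
- **Participants and power analysis** recruits from "four sports (curling, volleyball, i.e., indoor and beach, tennis, and hockey, i.e., floorball and ice hockey", and counts 36 athletes per group, 108 in all.
- The only provision for clustering, in **Statistical analysis**, is conditional: "If there are significant differences between different intervention sub-groups, we will perform multilevel analyses". The section on the interventions sets six sub-groups of six athletes in each condition.

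**The concern.** A group x time ANOVA on athletes treats each athlete's value as a separate piece of evidence. In a team sport, win/lose belongs to the team and the match. Every team-mate assessed in that match has the same value, and the allocation rule puts them all in one arm. The copies therefore shrink the apparent error of the arm mean without adding information.

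At stake is a claim that PST or MI changes winning, resting on a p-value computed as if there were far more independent results than there are. The method is stated, so this is not a detail left open for a later analysis plan.

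**Working it through.** **1. The plan's own figure.** With d = 0.6, one-sided α = 0.05 and 80% power, the normal approximation gives n = 2(1.645 + 0.842)²/0.6² = 34.4, so 35 per group. The exact t calculation gives power 0.7996 at 35 and 0.8095 at 36. The stated 36 per group reproduces, with each athlete counted as one independent unit.

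**2. The test.** The waiting-list arm is assessed only at T1 and T2 before it is re-allocated, so all three arms share two time points. With two time points, the group x time F test equals a one-way ANOVA on the change T2 − T1, here with 2 and 108 − 3 = 105 degrees of freedom. The 5% critical value is 3.083.

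**3. What copying does.** Suppose every athlete is in a team with m enrolled members who share one result at each time. There are then T = 108/m independent results. Copying multiplies the between-arm and within-arm sums of squares by the same m, but the denominator degrees of freedom stay at 105 instead of T − 3. Hence

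F(athletes) = F(teams) × 105/(T − 3).

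For 2 and v degrees of freedom, P(F > x) = (1 + 2x/v)^(−v/2). With v = T − 3 and x = 3.083 × (T − 3)/105, the rejection probability under no effect is (1 + 2 × 3.083/105)^(−(T − 3)/2). At T = 108 this is 0.05, so it simplifies to

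false-positive rate = 0.05^((T − 3)/105).

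This formula treats team changes as normal. A simulation of the actual binary result (20,000 null trials per row, 36 athletes per arm, win probability 0.5) agrees with it:

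| Enrolled per team (m) | Independent results (T) | Formula | Simulated |
|---|---|---|---|
| 1 | 108 | 0.05^(105/105) = 0.05 | 0.05 |
| 2 | 54 | 0.05^(51/105) = 0.23 | 0.23 |
| 3 | 36 | 0.05^(33/105) = 0.39 | 0.40 |
| 4 | 27 | 0.05^(24/105) = 0.50 | 0.50 |
| 6 | 18 | 0.05^(15/105) = 0.65 | 0.65 |

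**4. Mixtures with individual players (simulated).** With 12 individual players and 24 team athletes per arm, the rate is about 0.29, 0.39 and 0.53 for teams of three, four and six. With 18 individual players and three teams of six per arm it is about 0.46.

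**5. Does scale alone matter?** With independent athletes, the same test holds its level: 0.050 to 0.052 for binary data (win probability 0.3 to 0.9), 0.048 to 0.049 for counts (mean 0.5 to 3), and 0.049 for four sports in different units balanced over arms.

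**6. Pooling raw units.** Take change-score SDs of 10, 4, 8 and 1 for the four sports (assumed). For a standardised effect of 0.6 in both active arms, power is 0.74 on a standardised scale and 0.57 in raw units. The two sports with the largest SD supply (100 + 64)/181 = 91% of the variance.

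**7. The multilevel trigger.** Win/lose change was compared across the six sub-groups within each active arm at the 5% level. If team-mates are spread at random over sub-groups, the trigger fires in about 10% of null trials or slightly fewer. When it does not fire, the false-positive rate is unchanged (about 65% and 50% for teams of six and four). If each sub-group is exactly one team of six, it fires almost always.

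**The case against.** The strongest reply is that the plan does contain a clustering rule, and that six sub-groups of six is the same layout as the worst row of the table. If each sub-group were one team, the sub-groups would almost always differ on win/lose and the multilevel analysis would replace the ANOVA. That is fair, and on that layout the 65% would not be the final result. The article does not say that sub-groups are teams, however. The rule names intervention sub-groups, depends on a significance test, and has nothing to act on in the waiting-list arm, which receives no intervention before T2 although its teams share results too.

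A second reply is that the size rests on inputs that the article does not give. This also stands. The range runs from 5% to 65%, and assessing team-mates in different matches would lower it.

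A third is that the authors themselves regard objective performance as too remote to judge an intervention, and that their main conclusion concerns functional athletic behavior. That limits the consequence. It does not make the stated test valid for win/lose.

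A reader might go further and infer that the p-values for all objective indicators are wrong because they are binary, counts or in different units. Steps 5 and 6 do not support that: the level holds, and the harm from raw units is to interpretation and power. Nor do the documents show that a pooled indicator would mainly reflect which sports sit in which arm. Allocation is stratified by sport, and the test works on change, so stable differences between sports cancel. Pooling in raw units is itself an inference, because the article speaks of indicators relevant to each sport and does not say that they are averaged together. Goals/assists and winners/unforced errors can also be recorded per athlete, so the sharing problem applies mainly to win/lose.

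**Conclusion.** The point holds for win/lose in the team sports. As written, the ANOVA counts one team result once per enrolled team-mate. The false-positive rate at a nominal 5% is then about 23% for pairs, 50% for fours and 65% for sixes, and 5% if all are individual players. The first three figures assume that all athletes are in teams of that size and that team-mates are assessed in the same match; the simulated rates also assume a win probability of 0.5. That athletes are the unit is read from the sample size and from the absence of any team unit; the article does not state it outright. The conditional multilevel rule cannot be relied on to correct the test.

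For sport-specific indicators the conclusion is narrower: if they are pooled in raw units, the estimate is hard to interpret and power is lost. Only secondary outcomes are affected. The change is worth making because it is cheap and the error for win/lose can be large.

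**What to change.** In the Statistical analysis section, take win/lose out of the general ANOVA sentence. Analyse it with the team-match as the unit, or with a logistic mixed model or GEE clustered on team, whatever a test of sub-group differences shows. If sport-specific indicators are to be pooled, standardise them within sport first; otherwise report them by sport. Count models for goals or errors would be a reasonable preference, but nothing here requires them.

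The cost is a few sentences and no new data, provided that team and match are recorded for each athlete. The downside is wider uncertainty for win/lose, which reflects the number of independent results actually observed.
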